### Statistical analysis

2.14

Image data processing includes using methods such as independent component analysis (ICA) and function binding, applying professional software such as MRIcro for windows, Xjview 8.1, SPM 12, and Matlab 5.1.

Statistical analysis technique is used to apply a statistical test to the difference of prior-treatment and posttreatment, and to examine the curative effect difference within groups and among groups of all curative effect indexes. We will adopt the 2-sided test for all statistical tests. It is considered that the tested differences are statistically significant if *P* value is less than or equal to .05. If *P* value is greater than or equal to .05, the tested differences are not statistically significant. Details are as following.

Measurement data includes the *t* test will be adopted to run comparison among groups. When it does not comply with the normal distribution, we will choose Wilcoxon rank-sum test. Similarly, we will run paired *t* test toward the difference of prior-treatment and post-treatment, and it will be changed into Wilcoxon rank-sum test, while it does not comply with the normal distribution.

Enumeration data: We will use the Chi-square test, calibration Chi-square test, and Fisher exact method to run comparison among groups.

Ranked data: Wilcoxon rank-sum test will be applied to run comparison among groups and signed rank-sum test to run comparison within groups.

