### Trial design and study setting

2.2

This study is a parallel designed, exploratory randomized, controlled, assessor-statistician-blinded, positive medicine clinical trial. Seventy participants with PMOP will be randomly assigned to the treatment group (taking acupoint thread embedding treatment, n = 35) and a control group (taking Climen treatment, n = 35) in a 1 : 1 ratio. The trial design and study flowchart are shown in Fig. 1.

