#### Study schedule

2.9.1

The study schedule is presented in Table 1. At the screening visit, participants will sign the informed consent form. In a baseline questionnaire, the following information will be obtained: age, occupation (physical/nonphysical), education level, last menstrual period, previous use of acupuncture, and expectation to acupoint thread embedding treatment. Moreover, Short-Form of McGill Pain Questionnaire (SF-MPQ), Osteoporosis Symptom Score, Osteoporosis Quality of Life Scale (OQOLS), 16-item Assessment of Health-Related Quality of Life in Osteoporosis (ECOS-16) must be completed at the baseline (week 0). Thereafter, study subjects will be randomized. There is a 3-month study period and a 1-month follow-up period for each group. In the study period, SF-MPQ, OQOLS, ECOS-16, and Osteoporosis Symptom Score will be evaluated every 4 weeks. fMRI and bone density test will be tested 2 times: in week 0 and week 12.

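### Between-group tests carry no baseline adjustment and do not say whether post or change scores are compared; ANCOVA would be more precise either way.

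*Protocol article*

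**What the plan says.** The analysis is set out in section 2.14 (Statistical analysis) of the protocol article.

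- **Between groups, measurement data:** a t "test will be adopted to run comparison among groups". The fallback reads: "When it does not comply with the normal distribution, we will choose Wilcoxon rank-sum test".
- **Opening sentence of the analysis rules:** "Statistical analysis technique is used to apply a statistical test to the difference of prior-treatment and posttreatment". It goes on to mention effects within and among groups. The detailed rules below it give the pre-post difference to a paired t test, which is a within-group comparison.
- **Test level:** "We will adopt the 2-sided test for all statistical tests", with significance declared when the P "value is less than or equal to .05".
- **Size:** "Seventy participants with PMOP will be randomly assigned to the treatment group" or to "a control group (taking Climen treatment, n = 35) in a 1 : 1 ratio" (section 2.2).
- **Baseline data:** section 2.9.1 has the SF-MPQ, Osteoporosis Symptom Score, OQOLS and ECOS-16 completed at week 0, before randomisation, and then every 4 weeks in the study period. Sections 2.10 and 2.11 add the follow-up period.

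No covariate, ANCOVA, regression model or repeated-measures model is named in the article.

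**The concern.** Each patient's baseline score on the outcome scale is in hand before allocation, and it is usually the best single predictor of the later score. A two-sample t or rank-sum test has no term for it. If post scores are compared, the baseline information goes unused. If change scores are compared, it is used with a fixed coefficient of 1, which is the most precise choice only if the regression slope of outcome on baseline happens to be 1. Section 2.14 does not settle which variable is tested, so the precision of the main comparison is not fixed either.

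In a trial of 70 patients this bears on how wide the confidence interval is and how small a difference the trial can detect. The fallback to the rank-sum test adds a smaller difficulty. A normality check on the trial's own data decides whether the result is a comparison of means or of ranks, so the reported quantity is not settled in advance.

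**Working it through.** **No figure to reproduce.** The article gives 70 patients without an effect size, SD, power or dropout rate, so there is no stated calculation to check.

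**Inputs from the document:** 35 per arm, 1:1 (section 2.2); two-sided .05 (section 2.14); baseline scores on all four scales (section 2.9.1).

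**Assumptions, not in the document:** equal SD at baseline and outcome; a correlation r between them of 0.3, 0.5 or 0.7; 80% power for the detectable difference; a true difference of 0.5 SD for the power illustration; all 70 patients analysed.

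**Step 1. Variance of the treatment contrast, relative to a t test on post scores**

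- Post scores: 1
- Change scores: 2(1 − r)
- ANCOVA: 1 − r²
- ANCOVA relative to change scores: (1 − r²) / [2(1 − r)] = (1 + r)/2

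| r | Post | Change | ANCOVA | Cut vs post (r²) | Cut vs change ((1 − r)/2) |
|---|---|---|---|---|---|
| 0.3 | 1 | 1.40 | 0.91 | 9% | 35% |
| 0.5 | 1 | 1.00 | 0.75 | 25% | 25% |
| 0.7 | 1 | 0.60 | 0.51 | 49% | 15% |

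ANCOVA has the smallest variance in every row. Below r = 0.5, change scores do worse than post scores.

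**Step 2. Difference detectable with 80% power**

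From the noncentral t distribution with 35 per arm, the post-score t test detects 0.679 SD. The other two follow by multiplying by the square root of the variance factor.

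| r | Post | Change: 0.679 × √[2(1 − r)] | ANCOVA: 0.679 × √(1 − r²) |
|---|---|---|---|
| 0.3 | 0.68 | 0.80 | 0.65 |
| 0.5 | 0.68 | 0.68 | 0.59 |
| 0.7 | 0.68 | 0.53 | 0.49 |

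A normal approximation gives slightly smaller values (0.67 SD for post scores; 0.64, 0.58 and 0.48 SD for ANCOVA) and the same picture.

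**Step 3. Power for an assumed 0.5 SD difference (noncentral t, one degree of freedom spent on the covariate)**

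| r | Post | Change | ANCOVA |
|---|---|---|---|
| 0.3 | 54% | 41% | 58% |
| 0.5 | 54% | 54% | 66% |
| 0.7 | 54% | 76% | 82% |

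**Step 4. Equivalent sample size.** At r = 0.5, ANCOVA on 70 patients is worth 70/0.75 ≈ 93 patients analysed by either t test.

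**The case against.** **The opening sentence can be read as a change-score analysis.** A reader might infer from the named tests that the trial ignores its baseline data, and that a chance imbalance in baseline pain passes whole into the estimate. The document does not support that. The general sentence about the pre-post difference leaves room for change scores to be compared between groups, and change scores do subtract baseline. Both inferences would hold only for a post-score comparison. This objection stands, and it is why both readings are worked above.

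**The unadjusted test is valid.** Under randomisation neither t test is biased. This also stands: what is lost is precision.

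**The gain rests on an unknown correlation.** True. At r = 0.3 the gain over post scores is only 9% in variance, and at r = 0.7 the gain over change scores is 15%. The trial calls itself exploratory and states no power target for these figures to miss.

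**An analysis plan may add adjustment.** It may, and covariates are often left to one. But section 2.14 goes beyond silence: it names specific tests for the between-group comparison, and those tests have no baseline term.

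**The test switch is a rule written in advance.** It is, and its harm is not quantified here. It is a secondary reason to reword the paragraph.

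**Treatment expectation.** The baseline questionnaire records "previous use of acupuncture, and expectation to acupoint thread embedding treatment". A reader might infer that adjusting for expectation would deal with self-reported outcomes in unblinded participants. It would not. Expectation is recorded before randomisation, which balances it on average; as a covariate it may add some precision, but it cannot remove bias that arises from patients knowing their allocation.

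**Conclusion.** The point holds as a free improvement in precision. The between-group analysis named in section 2.14 is valid. It does not fix whether post or change scores are tested, and it is less precise than ANCOVA under both readings. For r from 0.3 to 0.7, the variance saved is 9% to 49% against post scores and 35% down to 15% against change scores. The detectable difference falls from 0.68 SD to between 0.65 and 0.49 SD in the first case, and from 0.80, 0.68 and 0.53 SD to 0.65, 0.59 and 0.49 SD in the second.

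That ANCOVA is at least as precise does not depend on the value assumed for r, apart from the trivial loss of degrees of freedom. The size of the gain does, and it also rests on equal SDs at the two times and complete data. None of this shows bias in the planned comparison.

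**What to change.** In section 2.14, replace the between-group rule for the SF-MPQ and the Osteoporosis Symptom Score, and likewise for the OQOLS and ECOS-16, with one of these:

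- ANCOVA of the week-12 score on treatment group, with the baseline score of the same scale as covariate; or
- a mixed model over the post-baseline visits with treatment-by-visit and baseline-by-visit terms, reporting the week-12 treatment contrast.

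Report the adjusted difference with its 95% CI. Handle skewness with a robust or bootstrap interval, so that the estimated quantity stays the same whatever the distribution looks like, and drop the switch to the rank-sum test for these scales.

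The cost is rewording and one or two degrees of freedom out of 68. No new data, visits or patients are needed. The article reports recruitment as still under way (section 3.1), so the change can be recorded before any comparison by group is made.

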### Outcome measure: primary outcomes

2.10

Outcomes will be evaluated using multiple indexes. The primary outcomes are measured by the following therapeutic indexes: Short-Form of McGill Pain Questionnaire (SF-MPQ), Osteoporosis Symptom Score during the observation period (3 months) and follow-up period (1 month). After baseline time, they will be tested at week 0, week 4, week 8 and week 12, and during the follow-up period.

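### The observed data choose between the t test and the rank-sum test, and nothing holds one between-group test per scale across visits

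*Protocol article*

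**What the plan says.** Section 2.14 of the protocol article states that for measurement data the t "test will be adopted to run comparison among groups". The next sentence gives the switch: "When it does not comply with the normal distribution, we will choose Wilcoxon rank-sum test". The section's general aim is "to examine the curative effect difference within groups and among groups of all curative effect indexes", so the rule applies to all efficacy scales. All tests are two-sided, and significance is declared when the P "value is less than or equal to .05".

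The primary outcomes section (2.10) names two scales, SF-MPQ and the Osteoporosis Symptom Score, and says that "they will be tested at week 0, week 4, week 8 and week 12, and during the follow-up period". Counting follow-up as one occasion, each scale has four post-baseline measurements. The trial design section (2.2) sets 35 participants per arm.

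The article does not name a normality check, its threshold, or what it is applied to (each arm, the pooled data, residuals or change scores). It does not say that a test, once chosen for a scale, is kept at the other visits.

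**The concern.** The t test compares means. The rank-sum test asks whether values in one arm tend to be higher than in the other. The two agree when one arm is a shifted copy of the other, but not in general. Under the written rule, the distribution of the collected scores decides which question is answered.

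The rule can be applied afresh to each scale at each visit. SF-MPQ could then be tested on means at week 4 and on ranks at week 12, with the change driven by a borderline normality verdict. A reader following one scale over time would be comparing results that do not address the same hypothesis, and could not have known beforehand which hypothesis would be tested.

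**Working it through.** The article gives no figure to reproduce: there is no effect size, SD or power statement. The check is how often the rule would change the test, and what that does to error rates.

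**From the article:** 35 per arm; four post-baseline measurements per scale; two-sided .05; t test by default, rank-sum if non-normal.

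**Assumed, because the article is silent:** Shapiro-Wilk at .05 in each arm, with either failure triggering the switch; correlation 0.6 between visits; the score distributions below. For a gamma distribution with shape k, skewness = 2/√k.

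**1. How often the test changes** (simulation, 3,000 trials per row). The last column is a hand check. If p is the chance of switching at one visit and visits were independent, P(mixed) = 1 − p⁴ − (1 − p)⁴. Correlation between visits should lower this.

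| Scores | Skewness | Rank-sum chosen at week 12 | Test differs across 4 visits | Hand check |
|---|---|---|---|---|
| Normal | 0 | 9.6% | 32% | 33% |
| Gamma, shape 12 | 2/√12 = 0.58 | 38% | 76% | 83% |
| Gamma, shape 6 | 2/√6 = 0.82 | 59% | 77% | 85% |
| Gamma, shape 3 | 2/√3 = 1.15 | 87% | 41% | 43% |

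For normal data the switching rate also follows directly: 1 − 0.95² = 9.75%. A separate set of 2,000-trial runs gave per-visit and mixed rates of 10% and 34% (normal), 49% and 81% (gamma shape 8), 58% and 77% (a right-skewed integer score from 0 to 45), 76% and 60% (shape 4), and 99% and 2% (shape 1.5). Mixing is most frequent under mild skew, where the verdict is least certain. It nearly vanishes under strong skew.

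**2. Sensitivity to the check.** A one-sample Kolmogorov-Smirnov check on pooled residuals, with estimated mean and SD, triggers in only 0.3% (shape 12), 1.1% (shape 6) and 5.5% (shape 3) of runs. By the same formula, mixed tests would then occur in at most about 1 − 0.997⁴ = 1.2%, 1 − 0.989⁴ = 4.3% and 1 − 0.945⁴ = 20% of trials (the p⁴ term is negligible).

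**3. Type I error when both arms share a distribution** (week 12, 2,000 runs; Monte Carlo standard error √(0.05 × 0.95/2000) ≈ 0.5 points).

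| Scores | Fixed t | Fixed rank-sum | Switched rule |
|---|---|---|---|
| Normal | 6.05% | 5.80% | 6.35% |
| Gamma 8 | 5.10% | 5.25% | 5.45% |
| Integer 0–45 | 4.90% | 4.65% | 5.10% |
| Gamma 4 | 4.20% | 4.40% | 4.65% |
| Gamma 1.5 | 4.60% | 5.20% | 5.20% |

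The switched rule is at most 0.6 points above either fixed test, which is about the size of the simulation noise.

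**4. Equal means and equal SDs, different shapes.** The switched rule rejects in 5.1% (gamma 12 versus normal), 6.3% (gamma 6 versus normal), 5.4% to 5.7% (gamma 1.5 versus gamma 6) and 7.8% to 8.4% (gamma 1.5 versus normal). The t test stays between 4.6% and 5.9%. So the two hypotheses do differ, but the excess is small.

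**The case against.** A t test with a rank-based fallback is conventional, the trial is labelled exploratory, and the practical effect is modest. Under a pure shift of 0.67 SD (an assumption) the t and rank-sum tests have nearly equal power, 78% versus 79% at gamma shape 12 and 78% versus 81% at shape 6, and reach different verdicts in only 6% to 7% of trials. The switching rates also depend heavily on a normality check that the article does not specify. All of this stands. It limits the size of the point, but it does not supply the missing rule that would keep one hypothesis per scale.

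A reader might infer more than the documents support in four ways:

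- **That switching inflates false positives.** It does not do so materially when the arms share a distribution. The 8% in the gamma 1.5 versus normal case belongs to the rank-sum test itself, which is chosen there in about 93% to 95% of runs. It is not caused by switching.
- **That equal means with different shapes can give 20% rejection.** That figure arises for gamma 1.5 versus gamma 6 scaled to mean 1, where the SDs are 1/√1.5 = 0.82 and 1/√6 = 0.41. With SDs equalised it falls to 5.4% to 5.7%, so it reflects a twofold difference in spread.
- **That the lack of a planned effect estimate is itself a defect.** The section mentions no estimate or interval for either test, and a condensed article may leave that to the analysis plan.
- **That results could not be compared across visits at all.** Given the power and agreement figures above, this is too strong.

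**Conclusion.** The point holds as a modest one that is cheap to put right. The article states a data-dependent choice of between-group test for all efficacy indexes and does not fix one test per scale over the visits. The harm is a hypothesis that is not set in advance and can change between visits.

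The frequency depends on the check used. With Shapiro-Wilk in each arm and a visit correlation of 0.6, tests would be mixed in about 32% of trials with normal scores and 76% to 77% with skewness 0.6 to 0.8. An insensitive check would bring the latter down to a few per cent. Repeating the check at each visit is the natural reading of the rule, but the article does not say so; nothing in it rules this out. Score distributions and correlation are assumptions throughout. The case does not rest on type I error: with equal means and SDs but different shapes, rejection is about 5% to 8%.

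**What to change.** Delete the normality-based switch for between-group comparisons and name one analysis per scale, used at every post-baseline visit whatever the scores look like. One suitable choice is a linear or repeated-measures model with the baseline score as covariate, reporting the mean difference with a 95% CI, and robust or bootstrap standard errors if scores are skewed. Keep the rank-sum test as a labelled sensitivity analysis.

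The chance of mixed tests for a scale then becomes zero by construction. The change is to analysis wording only, with no new data, visits or participants. The article describes recruitment as still open, so on its own account the change can be made before analysis. The downside is a small loss of power if scores prove very heavy-tailed, and the sensitivity analysis would show whether that matters.

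### The fallback for non-normal before-after measurement data is the Wilcoxon rank-sum test, which ignores the pairing; it should be the signed-rank test

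*Protocol article*

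**What the plan says.** All the relevant text is in the protocol article, Section 2.14 (Statistical analysis).

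- **Measurement data, between groups:** a t test. The fallback is "When it does not comply with the normal distribution, we will choose Wilcoxon rank-sum test".
- **Measurement data, before versus after:** the next sentence opens with a word that carries the same logic over and says "we will run paired" t tests on the pre/post difference. Its fallback is "it will be changed into Wilcoxon rank-sum test, while it does not comply with the normal distribution".
- **Ranked data:** the rank-sum test between groups, and "signed rank-sum test to run comparison within groups".
- **Level and sidedness:** "We will adopt the 2-sided test for all statistical tests", with significance declared if the P "value is less than or equal to .05".

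The section applies before-after testing, within and between groups, to all efficacy indexes. Section 2.2 gives the size: "Seventy participants with PMOP will be randomly assigned to the treatment group" or the control group, 35 in each. Each within-group test therefore has at most 35 pairs.

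**The concern.** The rank-sum test takes its reference distribution from two independent samples. Applied to one arm's pre and post values, it treats 35 women measured twice as 70 unrelated observations. The variance it assumes for the difference is then too large whenever a woman's two values are positively correlated, as repeated scores on the same person normally are.

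The tests that could be affected are the before-after comparisons of the two primary scales (SF-MPQ and Osteoporosis Symptom Score), the two quality-of-life scales and BMD. Each is affected only if it is handled as measurement data and judged non-normal. A real within-arm change could then be reported as non-significant. There is also a side effect. If normality is accepted in one arm and rejected in the other, one arm gets a paired test and the other an unpaired one, so equal changes could look different only because of the test.

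Section 2.8 assigns the analysis to separate, blinded personnel. A statistician who follows the text literally would run the wrong test.

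**Working it through.** **No figure to reproduce.** The article gives no power, effect size, SD or pre/post correlation. The wrong test name is visible from the text alone; the calculations below only size the consequence.

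**Inputs from the article:** 35 pairs per arm (Section 2.2, no dropout); two-sided 5% level (Section 2.14).

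**Assumed:** pre/post correlation ρ on the underlying normal scale, varied from 0 to 0.9; the shape of the data; the size of the shift.

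**Step 1: actual type I error, by formula.** Pairing shrinks the null SD of the rank-sum z statistic by about √(1−ρ), so

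actual α ≈ 2 × [1 − Φ(1.96/√(1−ρ))]

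- ρ = 0.3: 1.96/√0.7 = 2.343, α ≈ 1.9%
- ρ = 0.5: 1.96/√0.5 = 2.772, α ≈ 0.56%
- ρ = 0.7: 1.96/√0.3 = 3.578, α ≈ 0.03%

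**Step 2: actual type I error, by simulation.** 10,000 replicates per setting, for normal data and two lognormal runs (log SD 1):

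| ρ | Rank-sum | Signed-rank |
|---|---|---|
| 0 | 4.6–5.4% | 5.0–5.4% |
| 0.3 | 1.9–2.3% | 5.0–5.4% |
| 0.5 | 0.6–0.8% | 4.6–5.1% |
| 0.7 | 0.05–0.15% | 4.9–5.1% |

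Simulation and formula agree closely. The formula is slightly low at 0.7 because the test works on ranks, whose correlation is a little below ρ.

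**Step 3: power at a moderate effect.** The standardised paired effect is set to give a paired z test 80% power:

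d_z = (1.960 + 0.842)/√35 = 0.474, so shift = 0.474 × √(2(1−ρ)) SD

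This is 0.56, 0.47, 0.37, 0.30 and 0.21 SD at ρ = 0.3, 0.5, 0.7, 0.8 and 0.9. Power, rank-sum versus signed-rank:

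| ρ | Normal | Lognormal, multiplicative shift | Lognormal, additive shift |
|---|---|---|---|
| 0.3 | 63% vs 76% | 63% vs 69% | 99.8% vs 97% |
| 0.5 | 47% vs 76% | 47% vs 69% | 99% vs 97% |
| 0.7 | 21% vs 75% | 22% vs 67% | 97.5% vs 97% |
| 0.8 | 7% vs 76% | 8% vs 67% | 93% vs 97% |
| 0.9 | 0.3% vs 75% | 0.4% vs 67% | 67% vs 97% |

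In the first two models the loss is 6 to 13 points at ρ = 0.3 and 21 to 29 points at 0.5. It exceeds half from about 0.7: (75 − 21)/75 = 72% of the power for normal data. With the strongly skewed additive shift there is no loss up to 0.7.

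**Step 4: sensitivity.**

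- *Fixed shift of 0.5 SD, normal data:* 53% vs 81% (ρ = 0.5) and 54% vs 95.5% (ρ = 0.7). The loss at 0.7 is (95.5 − 54)/95.5 = 43%, under half because the paired test is near its ceiling.
- *Milder skew (log SD 0.6), multiplicative shift of 0.4 log SD:* about 34% vs 45% (0.3), 32% vs 57% (0.5), 29% vs 79% (0.7).
- *Same skew, additive shift of 0.4 raw SD:* about 64% vs 63% (0.3), 66% vs 76% (0.5), 70% vs 92% (0.7).

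**The case against.** **It may be a wording slip.** The ranked-data sentence uses the hybrid phrase "signed rank-sum test to run comparison within groups", so the authors know the paired test, and the word for signed may simply have dropped out of the earlier sentence. That is plausible. It does not cure the text, which names a specific and different test.

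**The reach is limited.** This stands. The comparison of embedding with Climen uses the t test or the rank-sum test on independent groups, which is appropriate. Within-arm change does not by itself identify a treatment effect, and the trial describes itself as exploratory.

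**The error is conservative.** This also stands. With positive correlation the P values are too large, so the slip does not manufacture claims of benefit.

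**The fallback may not be triggered.** The paired t test needs normal differences, not normal raw scores. Under the log SD 0.6 model a Shapiro test rejected normality of the differences in only about 45–60% of runs. The article also does not say which scales count as measurement and which as ranked data; for ranked data the within-group test is already the signed-rank one. So how often the error would bite is unknown.

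**A stronger reading is tempting:** that most of the power is lost. The article does not support it. It gives no pre/post correlation, distribution or effect size, and a loss of more than half appears only at about 0.7 or above under some of the models tried.

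**Conclusion.** The stated rule is wrong as written. An independent-samples test is named for paired data, and the section is inconsistent with its own treatment of ranked data. This conclusion needs no assumption.

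The size does rest on assumptions. With 35 complete pairs and correlations of 0.3, 0.5 and 0.7, the nominal 5% test rejects a true null about 2%, 0.7% and 0.1% of the time. The loss of power grows with the correlation, and its amount cannot be fixed from the article. A reader might also infer that the randomised treatment comparison is compromised; it is not, because the rank-sum test is the right fallback there. The point should be fixed, but it does not threaten the trial's main comparison.

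**What to change.** In the paired sentence of Section 2.14, replace the Wilcoxon rank-sum test with the Wilcoxon signed-rank test. Keep the rank-sum test for between-group comparisons only. It would help to use the same name in the ranked-data sentence, so that both within-group rules read alike, and to report the median paired difference with its 95% confidence interval beside the P value.

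The cost is one phrase in the analysis section, with no added patients, visits or data. In the simulations the signed-rank test held its level at 4.6–5.4% at every correlation tried.
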